### Qualitative Evaluation

A key aim of this study is to determine the acceptability and feasibility of the intervention delivery and evaluate whether and how this delivery could work as a service-level care pathway intervention for a future cluster randomised study. Therefore, the qualitative evaluation by both clinicians delivering the intervention as well as participants and carers receiving the intervention is key to assessing acceptability of intervention delivery. All interviews will be audio recorded with consent and transcribed verbatim.

### Qualitative Data for Uncertainties in Study Design

Reasons for non-completion of ENRICH reviews will be collected to inform the source of non-delivery of ENRICH reviews (eg, no time from clinical staff, participant refusal).

### Qualitative Data for Uncertainties in Intervention Delivery

Consenting healthcare professional participants will be invited to complete a custom survey and semi-structured interview about their feedback on contributing to ENRICH. The interview will focus both on barriers and facilitators to implementing ENRICH with patients who had a stroke and identify elements to maximise implementation of ENRICH reviews at the service level. We will probe for feedback on refining the ENRICH training for future healthcare professionals, experiences conducting ENRICH assessments and using the ENRICH workbook and how ENRICH is adopted into practice by those involved. We will aim to interview all consenting healthcare professionals and site principal investigators to maximise information gained.

Patients who had a stroke and carer participants consenting to research data collection will be invited to complete a custom post-study survey about their experience of ENRICH reviews at T2. In addition, a subset of purposively sampled stroke participants will be invited to complete a semi-structured interview on their experience of ENRICH reviews and study procedures. The topic guide will probe general experiences receiving ENRICH reviews, aspects that were helpful and not helpful, feedback on assessments used during reviews and using the ENRICH workbook. Carers will be invited to complete a semi-structured interview of their experience of ENRICH reviews and/or their perspective of the stroke survivor’s experience of ENRICH reviews, where we will probe their views on its helpfulness to the stroke survivor, the role of the family member in ENRICH reviews and its benefit beyond the review sessions themselves. Across all patients who had a stroke interviews, maximum variation sampling will be used to select a range of stroke severity, type of cognitive impairments (eg, language, memory, attention), participant sex, ethnicity and self-reported mood to enhance richness of the data and inform conclusions about acceptability.

### Qualitative Data for Uncertainties in Research Data Collection

In interviews, we will explore the acceptability of the candidate primary outcome measures (QOLIBRI and WHO-QOL-BREF) and the health economic measure (HEQ) given limited use of these measures in stroke. We will also explore acceptability of reviews being recorded for fidelity purposes.

From recruited sites, we will collect surveys on descriptions of usual care to inform what a future control arm would look like.

### Fidelity Data

As part of a process evaluation, fidelity to the intervention will be evaluated in two ways:

Healthcare professional-reported fidelity checklists of key components delivered of each ENRICH review.Audio recorded ENRICH reviews conducted with consenting stroke participants.

The above will inform whether the ENRICH intervention was delivered as intended and whether sufficient adherence can be achieved across recruited healthcare professionals.

The research team will also hold monthly meetings with local site champions (eg, clinical lead, principal investigator or senior therapists for service) and available healthcare professionals delivering the enhanced reviews to discuss any difficulties with implementation. Daily problem solving, if any, will be conducted in discussion with the principal investigator of recruited NHS stroke services. Any other adherence queries will be managed between the research team, site champion and principal investigator on a case-by-case basis.

### Sample Size

No formal sample size calculation was conducted. As the primary aim is to evaluate feasibility, we aimed to recruit up to 80 stroke survivors across sites (an average of 40 participants per site), allowing for 25% attrition. These numbers are in line with UK averages on sample sizes for feasibility studies.^30^ Assuming 50%–60% of stroke survivors will have a carer/family member who can take part we further aimed to recruit 45 carers (N=45 target), and 15 healthcare professionals. There are no planned interim analyses.

### Harm Monitoring

There are no outcome measures for harm monitoring, however we will monitor deaths, recurrent stroke, cognitive decline and worsening emotional symptoms of consenting patients who had a stroke using a customised survey following the end of participation of the stroke participant, completed by the staff at recruited sites.

### Participant Retention Plan

The research team will give up to three reminders to study participants to complete outcome assessments via email or telephone call within a month of their 6-month assessment window.

### Data Management

Data will be entered securely by recruited sites on Research Electronic Data Capture data management software. The research team will regularly download and anonymise data from recruited sites into a single cohesive dataset. Data audits on 10% of study data will be carried out to ensure data quality.

### Data Monitoring

An ENRICH advisory committee, comprising a PCPI representative and complex intervention and trial statistician expertise, will meet approximately triannually to oversee progress, advise on trial conduct and methodology.

### Quantitative Analysis

All quantitative data will be reported descriptively and will include all recruited participants. Rates of recruitment (numbers recruited per month, total numbers recruited, recruitment across participant categories), retention of sites and participants, number of ENRICH reviews delivered and number of patients receiving ENRICH reviews within the stroke service will be reported. Missing data will not be imputed.

Data on demographics (eg, age, sex, ethnicity, stroke severity) and study outcome measures at the post-ENRICH research visit will be summarised using descriptive statistics. Comparison of our recruited cohort to Sentinel Stroke National Audit Programme data, a UK quality improvement programme capturing national stroke outcomes, will be conducted to determine the generalisability of our cohort findings to the UK stroke population.

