### Uncertainties in Research Data Collection

It was unknown what the estimated completion rates and attrition would be for completion of the outcome measures, as well as uncertainty around which of two candidate quality of life outcome measures to use and whether health economic data could be captured adequately (see Outcomes for details on study measures). Further, it was unknown whether participants would find collecting fidelity data (see Fidelity section below) acceptable.

Taken together, we aimed to investigate acceptability and feasibility of the intervention delivery, as well as design feasibility of a future cluster design including waiver of consent for delivery of the ENRICH intervention. A summary of our key uncertainties and associated data we aim to collect is in table 1. Our qualitative aims with regards to delivering the intervention were to explore the acceptability of the ENRICH training by healthcare professionals and the ENRICH reviews by patients who had a stroke, carers and healthcare professionals through surveys and interviews. In addition, we will examine the fidelity to non-specific factors through audio recordings of reviews and explore barriers and facilitators of the implementation of the ENRICH reviews in clinical stroke services. With regards to study design, we aim to explore participants’ views on study procedures, materials and outcome measures, alongside understanding standard clinical care.

**Table 1 T1:** Summary of key uncertainties and associated data to be collected

Evaluation domain	Study component	Data source	Key uncertainty	Associated quantitative data	Associated qualitative data
**Feasibility**	**Study design**	Sites	Can we recruit sites?	Number of eligible sites expressing interest	
			How many patients receive ENRICH with waiver of consent?	Total number of reviews delivered	
			What is the standard of care?	Number of non-ENRICH clinical contacts	Descriptions of standard care across each recruited site
		Healthcare professionals	What is the most effective consent method?	Proportion consented by clinician role	
			Can we recruit and retain sufficient numbers?	Recruitment and attrition rates	
		Patients who had a stroke	Can we recruit and retain sufficient numbers?	Recruitment and attrition rates	
			Can we recruit a diverse sample?	Patient demographics vs national audit data	
			How many ENRICH reviews do participants receive?	ENRICH review completion rates	Reasons for non-completion

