### Participant Timeline

Stroke participant demographic data will be collected prior to the first ENRICH review at baseline (T1). Outcome data will be collected either via post, live via telephone/videoconferencing or using online surveys following completion of the final enhanced review at 6 months after stroke (T2; see table 3 for overview). Candidate outcomes were not collected at baseline as self-report assessments of quality of life were viewed not to be representative at time post-stroke of high emotional distress.

**Table 3 T3:** Overview of patients who had a stroke study outcome measures and additional data

	Baseline (T1)	Post-ENRICH assessment (T2)
Demographic information	✔	
Secondary outcome measures—candidate primary outcome measures for a future trial		
Quality of Life Instrument after Brain Injury		✔
WHO-Quality of Life Brief		✔
Process measures		
Patient Health Questionnaire-9		✔
Generalised Anxiety Disorder-7		✔
Modified Rankin Scale		✔
EQ-5D-5L		✔
Health Economics Questionnaire		✔
Additional data collection		
Custom post-study survey		✔
Semi-structured interview (~30% of participants)		✔

ENRICH, ENhanced Reviews of PsychologIcal Changes; EQ-5D-5L, EuroQol-5D-5Levels.

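### The national audit comparison on all recruited patients can support generalisability of the recruitment and feasibility findings, but not of the T2 results, which come from responders only

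*Protocol article*

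**What the plan says.** The Quantitative Analysis section names the group compared, "Comparison of our recruited cohort to Sentinel Stroke National Audit Programme data", and states the purpose: the comparison "will be conducted to determine the generalisability of our cohort findings to the UK stroke population". Table 1 lists the same comparison as "Patient demographics vs national audit data", under the question of whether a diverse sample can be recruited.

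The same section states "All quantitative data will be reported descriptively and will include all recruited participants", and also "Missing data will not be imputed". It lists age, sex, ethnicity and stroke severity as examples of the demographic data to be summarised.

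Under Participant Timeline, demographics are taken at baseline (T1), before the first review. Outcome data are collected "following completion of the final enhanced review at 6 months after stroke" (T2). Table 3 shows both quality of life measures, the process measures, the EQ-5D-5L, the Health Economics Questionnaire and the post-study survey at T2 only. The Sample Size section sets a target of up to 80 stroke survivors, "allowing for 25% attrition".

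**The concern.** The group checked against the audit is not the group that supplies the T2 results. The check uses data held on every recruit from T1, whereas the T2 summaries use only the patients who answer at 6 months. A close match to the audit therefore shows that the right patients were recruited. It says nothing about whether those who returned T2 data resemble the stroke population.

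Loss over six months after stroke is plausibly related to severity, cognition and mood, and these plausibly affect quality of life scores and helpfulness ratings. A report that follows the plan exactly could state that the cohort matches the audit and that its findings therefore generalise, while the more impaired patients are under-represented in the T2 summaries. Those summaries will be read when the choice of primary outcome and the design of the cluster trial are settled.

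No section compares T2 responders with non-responders or with the audit. The comparison with non-consenting patients raised under Uncertainties in Study Design concerns selection at recruitment, which is a different step.

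**Working it through.** **Inputs from the protocol article**
- Recruitment target 80, an average of 40 per site at two sites; attrition 25% (Sample Size).
- Outcome completion: green at 75% or more, amber from 50% to 75% (Table 4).
- Patient helpfulness: green when the mean is above 3.5 out of 5 (Table 4), taken from the T2 survey.
- Prevalence of depression and anxiety 25–30%; any cognitive impairment at 6 months up to 68% (Introduction).

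**The plan's own figures.** 2 × 40 = 80, as stated. The article gives no number of completers. It follows as 80 × (1 − 0.25) = 60. At 50% completion it is 80 × 0.50 = 40. This treats attrition as absence of T2 data and takes completion to be similar across T2 instruments.

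**Which results rest on which patients**
- All recruits: recruitment, retention, reviews received, completion rates, T1 demographics.
- T2 responders only: QOLIBRI, WHO-QOL-BREF, the T2 process measures, EQ-5D-5L, resource use, helpfulness and usefulness ratings.

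The audit comparison uses the first group, so its result is fixed before T2 and cannot change with who responds.

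**How far responders can differ from recruits.** Let p be a subgroup's share of recruits and R the ratio of its loss rate to that of the others (assumed), with overall loss 0.25.
- Loss in the others: a = 0.25 / ((1 − p) + pR)
- Share among responders: p(1 − Ra) / 0.75

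For p = 0.25:
- R = 1.5: a = 0.25/1.125 = 0.222; share = 0.25 × 0.667/0.75 = 22.2%
- R = 2: a = 0.25/1.25 = 0.200; share = 0.25 × 0.600/0.75 = 20.0%
- R = 3: a = 0.25/1.5 = 0.167; share = 0.25 × 0.500/0.75 = 16.7%

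Of 60 responders, 15 would be expected from this subgroup without selection (0.25 × 60). The three cases give about 13, 12 and 10.

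For p = 0.30 the shares are 27.0%, 24.6% and 21.2%. For p = 0.68 they are 65.3%, 63.7% and 61.9%, so the distortion is small for very common traits.

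**A case using severity, which is among the listed variables.** Assume 40% of recruits are severely affected and the audit share is also 40%. The recruited-cohort check then matches exactly in every row.

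| Completion, severe / other | Overall completion | Severe share of responders |
|---|---|---|
| 75% / 75% | 75% | 40% |
| 60% / 85% | 75% | 32% |
| 45% / 95% | 75% | 24% |
| 25% / 67% | 50% | 20% |

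Second row: 32 × 0.60 = 19.2 and 48 × 0.85 = 40.8; 19.2/60 = 32%.

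**Reading a helpfulness mean.** With completion c and observed mean m, the mean over all recruits would equal 3.5 if non-responders averaged (3.5 − cm)/(1 − c).
- c = 0.75, m = 3.6: (3.5 − 2.7)/0.25 = 3.2
- c = 0.75, m = 3.8: (3.5 − 2.85)/0.25 = 2.6
- c = 0.50, m = 3.6: (3.5 − 1.8)/0.50 = 3.4
- c = 0.50, m = 3.8: (3.5 − 1.9)/0.50 = 3.2

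The observed means are assumed. The gap needed to change the reading of a mean near the cut-off is small, particularly at 50% completion.

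**The case against.** The strongest reply is that the sentence is loosely worded and no more. Table 1 ties the comparison to recruiting a diverse sample, and the primary outcome is recruitment, attendance and completion. For those, all recruits are the right group. A responder table is also the kind of detail an unseen analysis plan may hold. The first part stands for the feasibility outcomes, and the recruited-cohort comparison should stay. The second part does not remove the point: the article fixes both the group compared and the conclusion to be drawn, and that conclusion is about the findings without restriction.

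Three stronger readings are tempting, and the documents do not support them.
- A reader might infer that an audit match helps the study pass to the next trial. It does not: the comparison has no threshold and does not appear in Table 4, where helpfulness is scored on its own cut-off.
- A reader might infer that the lack of imputation is the fault. It is an acceptable choice in a descriptive feasibility study.
- A reader might infer that response will be selective. Nothing in the article shows this, and every loss ratio and completion split above is assumed.

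Loss is not hidden either. Retention and completion rates are reported, and completion is a progression criterion. Patient interviews are sampled for variation in severity, cognitive impairment and mood. These show how many are lost and widen the qualitative picture, but they do not show how responders differ from those lost.

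The size also has limits. The standard error of a 25% share at n = 60 is √(0.25 × 0.75/60) = 5.6 percentage points. At R = 2 the subgroup would be 20% of 60 responders and 40% of 20 non-responders, with a 95% interval on the difference of about ±1.96 × √(0.16/60 + 0.24/20) = ±24 points. The extra table can describe but not test. The 25–30% figure concerns mood, which the audit comparison is not said to cover, so a repeated audit comparison alone might miss that kind of loss. The in-review scores in the responder table would address it.

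**Conclusion.** The point holds with a defined scope. A comparison of all recruits with the national audit supports statements about who was recruited and about the feasibility outcomes. It does not support a statement that the T2 results generalise, because those rest on about 60 of 80 patients at the planned attrition and on 40 of 80 at the bottom of the amber band. The sentence promising that all recruited participants are included likewise cannot hold for T2 summaries where data are missing.

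Under assumed loss ratios of 1.5 to 3, a 25% subgroup would fall to between 22% and 17% of responders, and the planned comparison would show none of it. No Table 4 colour depends on the audit comparison, so the effect is on how T2 results are interpreted. Importance is modest.

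**What to change.** In the Quantitative Analysis section:

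1. Keep the comparison of all recruited patients with the audit, and describe it as a check on representativeness of recruitment.
2. Repeat the same demographic and severity comparison for patients with T2 data, and base any generalisability statement about T2 results on that.
3. Add one descriptive table, without tests, of T2 responders against non-responders on T1 age, sex, ethnicity and stroke severity, plus first-review OCS, PHQ-9, GAD-7 and FSS scores where available. Show it beside the helpfulness mean.

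At minimum, limit the existing sentence to representativeness of recruitment.

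The cost is one table and a change of wording. The data are already to be collected, so no visits or patients are added. The drawbacks are small groups (about 60 and 20), in-review scores missing for patients who had no review, and a generalisability statement for T2 results that may be less favourable.

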### Qualitative Analysis

Results from the post-study survey will be summarised to determine whether patients who had a stroke and carers found the enhanced reviews helpful, relevant and whether information needs regarding post-stroke psychological needs were sufficiently met. We will similarly describe average ratings of helpfulness of ENRICH reviews from recruited healthcare professionals. Any changes required prior to the progression of a definitive trial based on acceptability data will be reported.

Qualitative data will be analysed using a framework analysis based on the Theoretical Framework of Acceptability (TFA^31^). The aim of the qualitative analysis will be to understand why and in what specific circumstances the intervention did or did not work and to identify potential ways to improve the intervention as a means of informing intervention acceptability. The research team will meet regularly throughout the transcription process to revise the analytical framework. Once all transcripts are coded, data will be charted in a framework matrix with candidate codes and participant quotes labelled by identification number, mapped against TFA components of affective attitude, burden, perceived effectiveness, ethicality, intervention coherence, opportunity costs and self-efficacy. The research team will reflect on the matrix and adapt it to represent other units of analysis (eg, clinicians vs participants, participants with cognitive impairment vs participants without cognitive impairment) to develop an understanding of intergroup similarities and differences in intervention perceptions across TFA domains. A final theme structure will then be constructed from the matrices that describes key barriers and facilitators to intervention delivery and potential modifications, if any, to be made for a future trial. In combination with helpfulness and usefulness ratings from participants, we will define acceptability as average helpfulness and usefulness ratings of at least 3.5 out of 5 on our custom survey and a smaller number of barriers reported in our framework analysis compared with perceived intervention benefits from patients who had a stroke and carers.

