		Family members	Can we recruit and retain sufficient numbers?	Recruitment and attrition rates	
Acceptability	Intervention delivery	Healthcare professionals	Can we train a variety of healthcare professionals to deliver ENRICH?	Numbers trained per site	Training survey feedback and interviews
			What are their views on ENRICH?	Helpfulness and usefulness ratings of ENRICH	Interviews on barriers and facilitators to ENRICH
			How many of those trained deliver the intervention?	Proportion of those trained delivering ENRICH	
		Patients who had a stroke	What are their views on ENRICH?	Helpfulness and usefulness ratings of ENRICH	Interviews on acceptability of ENRICH
		Family members	What are their views on ENRICH?	Helpfulness and usefulness ratings of ENRICH	Interviews on acceptability of ENRICH
	Research data collection	Patients who had a stroke and Site principal investigators	Which candidate primary outcome measure is best to use?	QOLIBRI and WHO-QOL-BREF completion rates	Interviews on acceptability of QOLIBRI and WHO-QOL-BREF
			Can we collect health economic information?	HEQ completion rates	
			Can we collect process outcome measures?	Process measure completion rates	
			Can we collect audio recorded fidelity data?	Proportion consenting to audio recordings	
Fidelity	Intervention delivery	Healthcare professionals	Are ENRICH intervention components delivered with high fidelity?	Completion checklists of intervention components; ratings of intervention audio recordings	

ENRICH, ENhanced Reviews of PsychologIcal Changes; HEQ, Health Economics Questionnaire; QOLIBRI, Quality of Life Instrument after Brain Injury; WHO-QOL-BREF, WHO-Quality of Life-Brief.

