### Quantitative Data for Uncertainties in Intervention Delivery

Our quantitative aims with regards to the delivery of the intervention are to investigate the numbers of trained clinicians delivering ENRICH reviews, proportions of recruited patients receiving ENRICH reviews and ratings of perceived helpfulness and usefulness (assessed using a custom Likert scale from 1 to 5) of ENRICH from healthcare professionals, patients who had a stroke and carers.

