### Study Progression Criteria

A priori defined progression criteria (table 4) will be used to determine whether the intervention can proceed to testing effectiveness in a cluster randomised controlled trial. These criteria were selected based on feasibility objectives, clinical assumptions and pragmatic expectations. If we do not meet targets in green, indicating that modifications are needed prior to progressing to an effectiveness trial, we will identify potential modifications from interview data described above with stroke participants, carers and healthcare professionals involved in ENRICH and agree on suitable modifications with the ENRICH advisory and PCPI committees. Final modifications will be discussed with the ENRICH advisory committee.

**Table 4 T4:** Progression criteria for ENRICH to a future effectiveness trial

Evaluation domain	Evaluation criterion	Green Proceed to trial	Amber Proceed to trial after modifications	Red Do not proceed to trial
Feasibility	Site recruitment	Two sites recruited within 6 months of REC approval.	Two sites recruited in more than 6 months since REC approval.	Unable to recruit sites.
	HCP recruitment	>50% of HCPs trained consented.	25%–50% of HCPs trained consented.	Less than 25% HCPs trained consented.
	Patients who had a stroke recruitment	Average >5 patients recruited per month.	Average 3–5 patients recruited per month.	<3 patients recruited per month by a site.
	Family member recruitment	>30% of recruited participants will have a family member who consent to provide outcome data.	10%–30% of recruited patients have a family member who consent to provide outcome data.	<10% of recruited patients have a family member who consent to provide outcome data.
Acceptability	ENRICH intervention delivery	≥50% of participants complete >1 ENRICH review.	30%–50% of participants complete >1 ENRICH review.	<30% of participants complete >1 ENRICH review.
	Outcome measure completion	≥75% completion of primary outcome measures (≥75%).	Moderate rates of completion of primary outcome measures (≥50%–75%).	Low rates of completion of primary outcome measures (<50%).
	Patients who had a stroke acceptability	Average rating of >3.5 out of 5 for helpfulness of ENRICH reviews.	Average rating of 3 out of 5 for helpfulness of ENRICH reviews.	Average rating less than 3 out of 5 for helpfulness of ENRICH reviews.

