	Intervention delivery	Qualitative data supports feasibility with minor modifications.	Qualitative data supports feasibility but with major modifications made.	Qualitative data does not support feasibility, even with major modifications.
Fidelity	Treatment fidelity	≥70% adherence ratings across sites.	50%–70% treatment fidelity across sites.	Less than 50% treatment fidelity across sites.

ENRICH, ENhanced Reviews of PsychologIcal Changes; HCP, Health Care Professional; REC, Research Ethics Committee.

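### Acceptability is defined on helpfulness and usefulness ratings, but the Table 4 progression row uses patients' helpfulness alone, so a study can be green on that row and still fail its own definition

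*Protocol article*

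**What the plan says.** The Qualitative Analysis section of the protocol article gives a two-part definition. The ratings part is "we will define acceptability as average helpfulness and usefulness ratings of at least 3.5 out of 5 on our custom survey". The second part is "a smaller number of barriers reported in our framework analysis compared with perceived intervention benefits from patients who had a stroke and carers".

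Table 4, under Study Progression Criteria, holds the pre-set criteria for going on to a cluster randomised trial. Its only ratings row is the one for acceptability to patients:

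- Green: "Average rating of >3.5 out of 5 for helpfulness of ENRICH reviews".
- Amber: "Average rating of 3 out of 5 for helpfulness of ENRICH reviews".
- Red: "Average rating less than 3 out of 5 for helpfulness of ENRICH reviews".

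A separate row on intervention delivery, also in the acceptability domain, is green if "Qualitative data supports feasibility with minor modifications".

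Usefulness is a planned measurement. Table 1 lists "Helpfulness and usefulness ratings of ENRICH" as quantitative acceptability data for professionals, patients and family members. The section on quantitative data for intervention delivery plans "ratings of perceived helpfulness and usefulness (assessed using a custom Likert scale from 1 to 5) of ENRICH from healthcare professionals", as well as from patients and carers.

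**The concern.** The two places set different rules for the same construct, on the same survey and at the same nominal cut of 3.5. The text uses two ratings and the table uses one. The text accepts a mean of exactly 3.5 and the table does not.

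The progression decision is what this feasibility study is for. If patients find the reviews helpful but not especially useful, the report could conclude from the same responses that ENRICH is not acceptable and that the acceptability row says to proceed. Nothing states which rule governs, so the choice could be made after the ratings are known.

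**Working it through.** **No figure to reproduce.** The Sample Size section states that no formal calculation was made, and the article gives no SD or correlation for the ratings. The check compares the two rules, first on fixed means and then under stated assumptions.

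**The rules.** Let H and U be the mean helpfulness and mean usefulness ratings.

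- Table 4 row: green if H > 3.5.
- Text, reading A (each mean): H ≥ 3.5 and U ≥ 3.5.
- Text, reading B (the two averaged): (H + U)/2 ≥ 3.5.

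The wording of the definition allows both A and B.

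**Fixed means (illustrative values).**

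| H | U | Table 4 row | Reading A | (H + U)/2 | Reading B |
|---|---|---|---|---|---|
| 3.8 | 3.0 | green | fails | 3.40 | fails |
| 4.0 | 2.9 | green | fails | 3.45 | fails |
| 3.8 | 3.4 | green | fails | 3.60 | passes |
| 3.5 | 3.5 | not green, no colour | passes | 3.50 | passes |
| 3.2 | 3.2 | no colour | fails | 3.20 | fails |

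The first two lines show that the contradiction does not depend on the reading. The fourth is the boundary mismatch. The fourth and fifth also show that, read literally, amber is the single value 3, so means above 3 and up to 3.5 have no colour.

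**How often.** Inputs:

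- n = 80 × (1 − 0.25) = 60 responders, from the recruitment target and attrition allowance in the Sample Size section.
- SD 1.1 for each rating and correlation r = 0.6 between them. Both are assumptions.
- Sample means are treated as bivariate normal.

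Standard error of each mean: 1.1/√60 = 0.142. Standard error of the average of the two: 0.142 × √((1 + 0.6)/2) = 0.127.

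True means 3.8 and 3.4:

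- P(green) = Φ((3.8 − 3.5)/0.142) = Φ(2.11) = 0.98.
- Reading A: P(U ≥ 3.5) = Φ((3.4 − 3.5)/0.142) = Φ(−0.70) = 0.24. The joint probability with H ≥ 3.5 is also 0.24. Conflict = 0.98 − 0.24 = 0.74.
- Reading B: P(average ≥ 3.5) = Φ((3.6 − 3.5)/0.127) = Φ(0.79) = 0.78. Conflict = 0.98 − 0.78 = 0.20.

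The same steps for other true means:

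| True H / U | Conflict, A | Conflict, B |
|---|---|---|
| 3.8 / 3.4 | 74% | 20% |
| 3.8 / 3.2 | 97% | 48% |
| 3.8 / 3.7 | 7% | 2% |
| 3.8 / 3.8 | 1% | 1% |
| 3.2 / 3.2 | 1% | 1% |

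With r = 0.8 the entries move by about one percentage point at most.

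**The case against.** The best defence is that Table 4 is not the only route by which poor usefulness could count. The Qualitative Analysis section promises to report changes needed before a definitive trial on the basis of acceptability data, and to draw possible modifications from the themes. The intervention delivery row of Table 4 rests on qualitative data, and the Quantitative Outcome Measures section classes the custom survey of carers and professionals as qualitative. Low usefulness, or unfavourable carer feedback, could therefore influence that row. The study is also single-arm and descriptive, with both ratings collected and open to view.

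Much of this stands, and it rules out some stronger conclusions that a reader might draw:

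- That usefulness and carer ratings have no effect on progression, or that only Table 4 can prompt modifications. The routes above contradict this.
- That the definition requires a carer rating of 3.5. Its mention of carers belongs to the comparison of barriers with benefits. A carer cut would be a new criterion.
- That the rules agree only when both means are well above 3.5. They also agree when both are well below it.
- That conflict is 74% or 97% without qualification. Those figures need reading A and a gap of 0.4 to 0.6 between the true means, which is assumed.

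The defence does not remove the mismatch. The qualitative row asks about feasibility and has no rating threshold, and nothing presents the patient row as a deliberate subset of the definition.

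**Conclusion.** The inconsistency is real. The ratings condition in the text and the patient acceptability row of Table 4 are different rules, and the row can be green when the definition fails under either reading. Green here means that row, not the whole table; an overall green remains possible because no other row tests a usefulness rating.

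That the rules can conflict needs no assumption. The frequency does: it ranges from about 1% to about 97% over the scenarios shown, driven by how far usefulness falls below helpfulness, where the means lie relative to 3.5, and which reading applies. Because the row informs the decision to proceed, the rule should be settled before the ratings are seen.

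**What to change.** Use one rating rule in both places.

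- In the patient acceptability row of Table 4, make green: patients' mean helpfulness and mean usefulness each at least 3.5.
- Make amber the range from 3 up to the green cut. With two ratings, that is both means at least 3 and at least one below 3.5, with red if either is below 3. Every result then has a colour; 3.8 with 3.0 or with 3.4 becomes amber. Changing green alone would leave such results without one.
- Have the Qualitative Analysis section refer to this row for its rating condition.
- If helpfulness alone is intended, remove usefulness from the definition instead, use the same inequality (≥ or >) in both places, and still make amber a range.

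A separate carer threshold is optional and is not needed to reconcile the two places.

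The cost is wording; both ratings are already planned. Green becomes slightly harder to reach: under the assumptions above, with both true means at 3.8, its probability falls from about 98% to about 97%. The loss is larger when usefulness is truly lower, which is what the definition intends.
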